## Abstract

**Background:**

HIV incidence among adolescent girls and young women (AGYW) aged 15-24 years in Eastern and Southern Africa remains unacceptably high. Unprotected sex increases the risk of HIV and other sexually transmitted infections and unintended pregnancies, reflecting an unmet need for effective contraception among AGYW. Long-acting injectable preexposure prophylaxis (LAI-PrEP) and long-acting reversible contraception (LARC) offer effective, durable protection against HIV and unintended pregnancy. However, uptake and persistence remain suboptimal due to low awareness, fear of side effects, stigma, limited decision-making autonomy, and poor integrated reproductive health and HIV prevention services. Evidence on community-driven and behaviorally informed strategies to support integrated rollout and uptake of LAI-PrEP and LARC among AGYW in Uganda remains limited.

**Objective:**

The study aims to determine the preferences and willingness of AGYW in Uganda to use LARC and LAI-PrEP, and characterize stakeholder perceptions, practices, and social norms that may influence adoption of integrated LARC and LAI-PrEP services. It applies the Capability, Opportunity, Motivation–Behavior (COM-B) model to identify facilitators and barriers to uptake and adherence.

**Methods:**

This mixed methods implementation science study, guided by the COM-B model and the Behavior Change Wheel (BCW), will be conducted in 3 Kampala Capital City Authority clinics to generate evidence and co-design community-driven strategies supporting integrated LARC and LAI-PrEP uptake among AGYW. The study will proceed in three stages: (1) structured surveys with 220 AGYW to assess determinants of uptake and willingness to use integrated services, (2) focus group discussions with 30 AGYW and in-depth interviews with 20 key informants to explore perceptions, preferences, and barriers, and (3) participatory co-design of behavior change strategies. Survey data will be analyzed using descriptive and multivariable regression methods, while qualitative data will undergo reflexive thematic analysis guided by Braun and Clarke. Findings will be integrated using a convergent mixed methods approach through triangulation and joint displays to identify factors influencing implementation of integrated LARC and LAI-PrEP services.

**Results:**

The study was funded in February 2026. Ethical approval was obtained from the Joint Clinical Research Centre Research Ethics Committee (JCRC IRB/EC; JCRC-2025-143), Kampala Capital City Authority (DPHE/KCCA/1302/01), and the Uganda National Council for Science and Technology (UNCST; HS6232ES). Written informed consent was obtained from all participants. Study preparation, including staff training, development of study materials, and community sensitization, was completed before participant recruitment. Participant recruitment began in March 2026, and was completed in July 2026, with 220 AGYW and 20 key informants enrolled. Data cleaning and quality assurance are ongoing, with quantitative and qualitative analyses planned following completion of all study activities. Findings are anticipated to be reported in 2027.

**Conclusions:**

Findings will provide evidence-based recommendations to inform the targeted interventions and policy guidelines for scaling up integrated LARC and LAI-PrEP services.

**International Registered Report Identifier (IRRID):**

PRR1-10.2196/88635

## Introduction

### Background

Adolescent girls and young women (AGYW) in sub-Saharan Africa (SSA) face a dual burden of unintended pregnancies and HIV, which significantly impacts their health, educational attainment, and socioeconomic opportunities [1]. Uganda has one of the highest fertility rates globally (4.3 children/woman) [2,3], with a substantial proportion of pregnancies occurring among AGYW [4-6]. Concurrently, this demographic accounts for a disproportionate number of new HIV acquisitions driven by gender-based violence, early marriage, transactional sex, limited access to sexual and reproductive health (SRH) services, stigma, and socio-economic disparities [7-10]. In Uganda, HIV prevalence among AGYW aged 15-24 years is 9.1%, with an estimated 11,000 of the 37,000 new HIV acquisitions in 2024 [11] occurring in this age group [8]. Across SSA, HIV incidence among AGYW remains high, approximately 3.92 per 100 person-years, highlighting the urgent need for targeted prevention strategies, including preexposure prophylaxis (PrEP), comprehensive SRH services, and community-driven interventions addressing structural and behavioral risk factors [12]. Despite the availability of effective HIV prevention tools such as oral PrEP, uptake and adherence remain suboptimal among AGYW due to stigma, forgetfulness, limited awareness, and constrained service delivery models [13-16]. Structural barriers within the health system further compound these individual and social challenges.

Delivering HIV prevention services effectively in public health settings is often complicated by health system barriers, including limited provider training, stock-outs of essential commodities, and stigma associated with PrEP [14,17]. At the same time, unintended pregnancies remain a persistent challenge, reflecting gaps in contraceptive access, knowledge, cultural norms, financial constraints, and limited decision-making autonomy among AGYW [5,18-22]. Leveraging established health care platforms, such as family planning clinics and other youth-friendly service points, offers an opportunity to integrate HIV prevention and reproductive health services, making care more accessible and acceptable to AGYW.

Long-acting interventions, including long-acting reversible contraception (LARC) and long-acting injectable preexposure prophylaxis (LAI-PrEP), offer promising, durable protection against unintended pregnancy and HIV acquisition among AGYW [15,16,23-29]. Integrating these services within existing, youth-friendly, community-based platforms, such as family planning clinics, could overcome logistical and social barriers, improve uptake, adherence, and reproductive health outcomes, and help normalize preventive health behaviors [30-39]. Successful integration requires understanding AGYW preferences and engaging key stakeholders, including peers, parents, partners, community leaders, and health care providers, to ensure services are youth-friendly, acceptable, and responsive to community needs [40-43]. Community-centered, behaviorally informed approaches that leverage trusted influencers have been shown to improve access, acceptability, and adherence to health interventions, including HIV prevention [44,45], aligning with World Health Organization (WHO) and Joint United Nations Programme on HIV and AIDS (UNAIDS) recommendations for community-led strategies as essential for achieving universal health coverage and the 95-95-95 HIV targets by 2030 [7,46,47]. Understanding community perspectives, preferences, and norms is critical to designing effective behavior change strategies that support integrated service delivery. In this protocol paper, we describe an implementation study designed to evaluate community-driven strategies to optimize the uptake and adoption of integrated LARC and LAI-PrEP services among AGYW in Uganda.

### Conceptual Framework

Addressing the barriers to integrated LARC and LAI-PrEP uptake requires a systematic understanding of the behavioral and context-specific factors that influence service use. The Capability, Opportunity, Motivation-Behavior (COM-B) model and the Behavior Change Wheel (BCW) frameworks [48,49] provide this theoretical foundation by identifying determinants of behavior and linking them to appropriate intervention functions and implementation strategies. This model posits that behavior (in this case, uptake and adherence to integrated LARC and LAI-PrEP services) results from the dynamic interaction of Capability, Opportunity, and Motivation: (1) Capability encompasses AGYW’s knowledge, skills, and self-efficacy to use LARC and LAI-PrEP correctly and consistently, (2) Opportunity refers to external factors such as access to youth-friendly health services, provider support, peer influence, and community norms that facilitate or hinder uptake, (3) Motivation includes the internal processes that drive decision-making, such as perceived risk of HIV, attitudes toward contraception and PrEP, and willingness to use dual methods. These constructs are interlinked and inform each stage of study design, from participant recruitment and data collection tools to analysis and interpretation. The BCW will complement the COM-B model by identifying potential intervention functions (eg, education, persuasion, and enablement) and policy levers that can be used to address identified barriers and strengthen facilitators to uptake and adherence. The adapted conceptual framework for the COMPASS study is presented in Figure 1 [49], illustrating how COM-B components interact to influence behavioral outcomes related to the adoption of integrated LARC and LAI-PrEP services among AGYW in Uganda.

**Figure 1 figure1:**
[figure not shown]
Adapted Capability, Opportunity, Motivation-Behavior (COM-B) model and the Behaviour Change Wheel (BCW) conceptual framework for the COMPASS study. The figure illustrates how Capability, Opportunity, and Motivation interact to influence uptake of integrated long-acting reversible contraception and long-acting injectable preexposure prophylaxis services among adolescent girls and young women in Uganda and how these behavioral determinants inform the development of behavior change strategies. This figure was generated using an artificial intelligence tool (OpenAI DALL·E). Prompt used: “Create a simple, non-photorealistic diagram illustrating the COM-B model (Capability, Opportunity, Motivation → Behavior) adapted for the COMPASS study.” Source link to the generated image [50]. AGYW: adolescent girls and young women; LARC: long-acting reversible contraception; LAI-PrEP: long-acting injectable preexposure prophylaxis.

### Objectives

This study seeks to understand the uptake and adoption of integrated LARC and LAI-PrEP services among AGYW aged 15-24 years in Uganda, to inform community-driven strategies to optimize service delivery.

Specifically, the study aims to (1) determine AGYW preferences for and willingness to use LARC and LAI-PrEP, and (2) characterize stakeholder perceptions, practices, and norms, including those of AGYW peers, social media influencers, health care professionals, community leaders, and representatives from reproductive health and HIV prevention organizations that influence the adoption of integrated LARC and LAI-PrEP services.

## Methods

### Study Design

The COMPASS study will use a mixed methods, cross-sectional implementation science design. This study will use 3 data collection approaches (structured surveys, focus group discussions [FGDs], and in-depth interviews [IDIs]) to generate both quantitative and qualitative evidence on integrated LARC and LAI-PrEP services. Initially, quantitative data will be collected through structured surveys administered to AGYW attending selected health facilities in Kampala to assess their attitudes, preferences, and willingness to use LARC and LAI-PrEP (Multimedia Appendix 1). Qualitative data will be gathered through FGDs among a subset of surveyed AGYW to explore further perceptions and motivations influencing uptake in a group setting (Multimedia Appendix 2), and through IDIs with key stakeholders, including health care providers, community leaders, and program implementers, to provide detailed perspectives on the social, cultural, and health system factors that may influence the adoption of integrated services. Taken together, these approaches provide a layered understanding of both AGYW’s preferences and the broader contextual factors shaping uptake (Multimedia Appendix 3).

### Study Setting

The study will be conducted at 3 Kampala Capital City Authority (KCCA) clinics that currently provide both oral PrEP and LARC services: Kisenyi, Kawaala, and Komamboga Health Centers. Kisenyi Health Center, located in the heart of central Kampala, serves a densely populated urban area and primarily serves low-income AGYW who often face stigma, financial barriers, and limited access to reproductive health services. This urban setting enables the examination of health care preferences and barriers that are specific to densely populated city environments. Kawaala Health Center, located in a periurban area, serves communities that experience both urban and rural dynamics. AGYW in this catchment frequently encounter transportation challenges, reduced access to health care facilities, and socio-economic inequalities. Studying this periurban context provides critical insights into the barriers faced by AGYW in areas where health care needs are growing, but access remains limited. Komamboga Health Center, located on the northern outskirts of Kampala, serves a suburban population. AGYW in this area navigate challenges, including limited health care infrastructure and cultural barriers to adopting contraceptive and HIV prevention services. This suburban context provides a contrasting perspective to urban and peri-urban settings. These health centers were chosen due to their existing maternal and reproductive health programs, including youth-friendly services, making them ideal sites for piloting the integration of LARC and LAI-PrEP services in future interventions. Their diverse urban, suburban, and periurban contexts will enable the study to capture a representative range of AGYW experiences, challenges, and cultural contexts. Collectively, the findings from these centers are expected to generate actionable evidence to inform scalable models for integrating LARC and LAI-PrEP services across Uganda.

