### Sample Size and Sampling Procedures

The quantitative sample size of up to 220 AGYW was estimated using the Kish-Leslie formula [51], assuming an 85% acceptability of LARC and LAI-PrEP if these services were made available. This sample size enables robust estimation of preferences, attitudes, and willingness to use integrated services, while accounting for variability in uptake across the study population. Participants will be purposively selected from the three KCCA clinics to ensure representation across urban, suburban, and peri-urban settings. For FGDs, a subset of 30 AGYW who completed the quantitative survey will be selected using stratified purposive sampling to ensure diversity in age, LARC and PrEP experience, and socio-demographic characteristics. This approach will enable in-depth exploration of factors influencing uptake and adherence. KIs will also be purposively sampled to capture a wide range of perspectives, professional roles, and influence over reproductive health and HIV prevention services. This combined sampling approach ensures a comprehensive understanding of both individual-level experiences and community-level factors affecting the integration and uptake of LARC and LAI-PrEP among AGYW in Uganda.

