### Data Collection

Quantitative and qualitative data will be collected sequentially to capture individual-level, social, and structural factors influencing integrated LARC and LAI-PrEP service delivery. Acceptability of integrated services, our primary outcome, will be measured using structured questionnaires that include Likert-scale items assessing willingness to use, perceived suitability, and compatibility with existing norms and values. The questionnaire was developed using the COM-B model and the BCW [48,49] and includes domains assessing health behaviors and preferences, interest and intent to use LARC and LAI-PrEP, perceived acceptability, barriers and facilitators, likelihood to recommend, and behavioral readiness. Perceived acceptability will be assessed using three four-point Likert-scale items evaluating whether (1) LARC fits within participants’ personal, cultural, and social context; (2) participants feel comfortable using LAI-PrEP within the community; and (3) perceived social acceptability among peers. Responses will be scored from 1 (Strongly Disagree) to 4 (Strongly Agree), with higher scores indicating greater acceptability. A composite acceptability score will be calculated by summing responses across these items. For descriptive analyses, acceptability scores will also be categorized into higher and lower acceptability using the observed median composite score of the study as the threshold. Other questionnaire domains will be analyzed individually to characterize interest, preferences, behavioral readiness, and perceived barriers and facilitators to integrated LARC and LAI-PrEP services. The complete survey questionnaire has been provided in Multimedia Appendix 3. Structured questionnaires, discussion guides, and interview tools are designed to assess sociodemographic characteristics, reproductive health history, HIV prevention behaviors, knowledge, attitudes, and perceived barriers and facilitators. Table 2 summarizes the key study domains, data sources, and participant groups.

**Table 2 table2:** COMPASS study measures, data collection methods, and participant groups.

Domain or measure	Description or examples	Data source and method	Participants
Sociodemographic factors	Age, education, marital status, residence, employment status	Structured questionnaire	AGYW^a^
Reproductive and sexual health history	Parity, contraceptive use, fertility intentions, pregnancy history	Structured questionnaire	AGYW

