Logistic regression models will be used to identify predictors of high acceptability and willingness to use integrated LARC and LAI-PrEP services. Variables considered clinically or theoretically relevant, together with those demonstrating an association at the bivariate analysis stage (*P*<.20), will be considered for inclusion in the multivariable models. Potential confounders, including age, education, socioeconomic status, marital status, prior contraceptive use, and HIV prevention history, will be retained in the final models where appropriate, based on subject-matter knowledge and statistical significance. Multicollinearity among independent variables will be assessed using variance inflation factors (VIFs) and correlation matrices. Where scientifically justified, interaction effects (for example, between age group and prior contraceptive use) will be explored by including interaction terms in the regression models. Model fit and assumptions will be evaluated using appropriate diagnostic procedures, including goodness-of-fit tests and assessment of influential observations. Adjusted odds ratios (aORs) with 95% CIs will be reported, and statistical significance will be assessed at a 2-sided α level of .05. Comparative analyses using 2-tailed *t* tests or ANOVA will further explore differences in preferences and attitudes across subgroups, including younger (15-19 years) versus older (20-24 years) AGYW and rural versus urban participants. For clarity of interpretation, results will be presented in tables summarizing numerical data and key statistics, including odds ratios (ORs) and *P* values. They will be visually illustrated with bar charts, pie charts, and histograms. Clustered bar charts and box plots will be used to highlight subgroup differences and significant predictors. This combined descriptive, inferential, and visualization approach will provide a robust understanding of AGYW preferences and attitudes toward LARC and LAI-PrEP, identify key facilitators and barriers to their uptake, and reveal demographic and behavioral predictors of positive engagement with these prevention methods.

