Participant recruitment may also be subject to selection bias because clinic-based recruitment may preferentially enroll AGYW who are already engaged with health services, while peer-led snowball sampling may overrepresent individuals within existing social networks. To reduce this potential bias, the study incorporates community-based recruitment through peer networks, community health workers, community sensitization activities, and outreach beyond clinic settings, in addition to recruitment across three KCCA clinics that serve different populations: Kisenyi (urban), Kawaala (peri-urban), and Komamboga (suburban). Although these approaches are intended to broaden participant representation, some residual selection bias may remain.

Additionally, reliance on self-reported measures regarding sexual behavior, contraceptive use, and PrEP adherence may be affected by recall and social desirability bias [73-75]. Mitigation strategies, including confidential data collection methods and triangulation across multiple data sources, are built into the design to reduce these risks. Nonetheless, these limitations provide opportunities for future work, including follow-up studies to assess the applicability of identified strategies in rural contexts and longitudinal evaluations to determine their impact on sustained uptake and adherence. Future directions will also include pilot testing of co-designed interventions to refine their feasibility, cost-effectiveness, and scalability across diverse service delivery settings.

The evolving global HIV prevention funding and policy landscape further reinforces the significance of this research. Recent reductions and policy shifts in funding for the President’s Emergency Plan for AIDS Relief (PEPFAR) and the United States Agency for International Development (USAID) have heightened the emphasis on cost-efficiency, sustainability, and local ownership in HIV programming [76,77]. Although this study is not expected to be directly affected by these funding shifts, its focus on community-driven and contextually relevant implementation approaches aligns with global priorities to optimize resources and strengthen health systems.

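### Each setting type rests on a single clinic, so the design cannot show that barriers found at the urban clinic are specific to an urban setting

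*Protocol article*

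**What the plan says.** The Study Setting section of the protocol article states: "The study will be conducted at 3 Kampala Capital City Authority (KCCA) clinics that currently provide both oral PrEP and LARC services". It describes Kisenyi as the central urban site, Kawaala as peri-urban and Komamboga as suburban. The limitations text under Anticipated Findings repeats the same one-to-one pairing.

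What is claimed differs by site:

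- Urban: "This urban setting enables the examination of health care preferences and barriers that are specific to densely populated city environments".
- Peri-urban: "Studying this periurban context provides critical insights into the barriers faced by AGYW in areas where health care needs are growing", with the added remark that access there is still limited.
- Suburban: "This suburban context provides a contrasting perspective to urban and peri-urban settings".

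Sample Size and Sampling Procedures relies on the same three sites: "Participants will be purposively selected from the three KCCA clinics to ensure representation across urban, suburban, and peri-urban settings".

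In Data Analysis, t tests or ANOVA "will further explore differences in preferences and attitudes across subgroups". The two examples named are the two age bands and rural versus urban participants. Table 2 lists the sociodemographic items recorded for each woman as "Age, education, marital status, residence, employment status"; the categories of residence are not given.

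**The concern.** Setting type and clinic are the same variable here. Anything else that distinguishes the clinics travels with the setting label. The article itself describes such differences: a mainly low-income clientele at Kisenyi, transport difficulties around Kawaala, limited infrastructure and cultural barriers around Komamboga. With no second clinic of any type, nothing in the data can separate these from urbanicity.

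What is at stake is attribution. If young women at Kisenyi and Komamboga answer differently, the Study Setting text invites the reader to call the difference a property of dense city environments, when it may belong to one clinic and its clientele. A significance test would not guard against this, because its error term would be the variation between women and would leave out the variation between clinics of the same type.

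**Working it through.** **The plan's own figure.** The article gives no number for setting comparisons, so there is none to reproduce. Its sample size of 220 plays no part in the structural argument. It cannot be rebuilt from the stated inputs alone because the precision is not given: at 85% and an assumed precision of ±5 points, n = 1.96² × 0.85 × 0.15 / 0.05² = 196, and an assumed 10% loss gives 196 / 0.9 = 218. That is close to 220, and I do not call it wrong.

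**Step 1: structure.** Three setting types (Study Setting) with k clinics each leave 3(k − 1) degrees of freedom for clinic variation within a setting.

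| Clinics per setting | Degrees of freedom |
|---|---|
| 1 (this study) | 0 |
| 2 | 3 |
| 3 | 6 |

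With zero degrees of freedom, setting and clinic effects are not separately estimable. The number of women does not enter this result.

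**Step 2: illustration of size.** Inputs from the article: 220 women, three clinics, 85% (the sample-size assumption), two-sided 5%. My assumptions: an equal split (220 / 3 = 73.3 per clinic), no true setting effect, and a between-clinic SD s that the documents do not give.

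- Standard error used by an ordinary two-clinic comparison: √(2 × 0.85 × 0.15 / 73.3) = 5.9 points.
- Actual SD of the difference once clinics vary: √(5.9² + 2s²).
- Rejection rate: 2 × [1 − Φ(1.96 × 5.9 / actual SD)].

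| Assumed s (points) | Actual SD of difference (points) | Rejection at nominal 5% | ICC implied, s² / (0.85 × 0.15) |
|---|---|---|---|
| 0 | 5.9 | 5% | 0 |
| 2.5 | 6.9 | 9% | 0.005 |
| 5 | 9.2 | 21% | 0.020 |

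**Step 3: sensitivity to the proportion.** The 85% is a planning input. The categorised acceptability outcome is cut at the observed median, so its proportion may lie nearer 50%. At 50% the standard error is √(2 × 0.5 × 0.5 / 73.3) = 8.3 points, and the same formula gives about 7% at s = 2.5 and 14% at s = 5. The inflation is smaller but in the same direction.

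**Step 4: does recruiting more help?** With unlimited women per clinic the sampling error disappears, but the difference between two clinics still has SD √2 × s, which is 3.5 points at s = 2.5 and 7.1 points at s = 5.

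**Step 5: is it acknowledged?** The limitations cover transfer to rural areas, selection bias and self-report. They do not say that setting and clinic are inseparable. The three differing clinics are cited there as a way of reducing selection bias.

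**The case against.** The strongest reply is that the Study Setting text is a rationale for choosing sites. Purposive choice of contrasting sites is normal in a mixed methods study, and the wording about specificity is used only for the urban clinic; the peri-urban and suburban sentences are softer. The stated objectives contain no setting comparison, the focus groups are stratified by age, and strategies are derived by mapping barriers to the behavioural model with stakeholders. The article also says it is not aiming for external validity. All of this stands and limits the weight of the point. It does not rescue the urban sentence, because attributing a clinic difference to urbanicity is an error about the study's own data, before any question of generalising.

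Three stronger readings are tempting, and the documents do not support them.

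- A reader might infer that an ANOVA across the three settings is planned and will be inflated. No such test is named. The only location contrast given is rural versus urban participants. It shares the problem if location is assigned by clinic, but the article does not say that it will be.
- A reader might infer that staff, services and outreach differ between the clinics. The article does not say so: it gives youth-friendly services as a shared reason for choosing the clinics, and describes one recruitment approach for all. What it documents are differences in clientele and catchment.
- A reader might infer that chance clinic differences will be turned into setting-specific strategies. The article describes no such step.

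**Conclusion.** The point holds as a minor one. One clinic per setting type means that a clinic-defined setting difference is a difference between three clinics, and the statement about barriers specific to dense city environments claims something the design cannot deliver. This part rests only on the article's own site descriptions and needs no assumption.

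The size is illustrative. Rejection of about 9% to 21% for a two-clinic comparison depends on an assumed between-clinic SD of 2.5 to 5 points, equal clinic sizes and a proportion of 85%; at 50% it would be about 7% to 14%. None of these rates describes an analysis that the article commits to. The primary outcome, the sample size and the objectives are untouched.

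**What to change.** 1. In Study Setting, describe the three sites as contrasting clinics and remove the claim that findings at Kisenyi are specific to an urban environment.
2. Report any difference among sites as a between-clinic difference, and add to the limitations that clinic and setting type cannot be separated.
3. For the rural-urban comparison in Data Analysis, classify each woman by her own recorded residence. Look first at how residence is distributed within each clinic. If it varies enough, adjust for clinic, so that the contrast comes from women at the same clinic. If it does not, present the comparison as descriptive. Which case applies cannot be told from the article, because the residence categories are not given.

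The cost is weaker statements about setting and a little extra analysis of data already collected. The article reports that data collection is complete and the analyses are still to come, so no clinic can be added, but the wording and the rule for the location comparison can be settled before results are seen.
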